### Examination Modalities

#### PET Imaging and Quantification of 5-HT_4_R Brain Binding

PET scans are conducted using a high-resolution research tomography Siemens PET scanner (CTI/Siemens, Knoxville, TN, USA) (256 × 256 × 207 voxels; 1.22 × 1.22 × 1.22 mm). Participants are positioned uniformly in spine position and a specialized head holder is applied to reduce head motion during the scan. All participants undergo a 6 min transmission scan and are given an intravenous bolus of approximately 600 MBq of the PET tracer ligand [^11^C]SB207145. The bolus is administered over 20 s followed by a 120-min dynamic PET data acquisition. The radioligand is synthesized immediately prior to injection as described elsewhere (79).

#### Preprocessing and PET Quantification

The 120 min dynamic PET acquisitions are reconstructed into 38 time frames (6 × 5 s, 10 × 15 s, 4 × 30 s, 5 × 2 min, 5 × 5 min, and 8 × 10 min) using a 3D-OSEM PSF algorithm (16 subsets and 10 iterations) (80) and TXTV-based attenuation correction (81). For motion correction, the AIR 5.2.5 software will be used (82), aligning each PET frame to the first 5-min frame. Structural 3-Tesla MRI scans will be used for co-registration of the PET images with SPM8 software. Automatic delineation will be carried out in a user-independent manner in PVElab software (83) and mean tissue time activity curves for grey matter volumes will be extracted for kinetic modeling. No partial volume correction will be performed because of the high resolution of the scanner. Regions of interest (ROI) have been chosen due to their known relevance in mood disorders and abundance of 5-HT_4_R density (84). The selected ROIs for the primary analyses are neocortex, putamen, caudate nucleus and hippocampus. Co-registration and correct ROI placement for all subjects will be inspected in three planes by a trained investigator. PMOD version 3.0 (PMOD, Zurich, Switzerland) will be used for kinetic modeling and quantification of the 5-HT_4_R binding is performed using non-displaceable binding potential (BP_ND_) as the final outcome measure. The simplified reference tissue model will be used with cerebellum (excluding vermis) as reference region which previously has been validated in humans (76). BP_ND_ is defined as:

$$BP_{ND}=\frac{f_{ND}\times \text{Bavail}}{KD}$$

where f_ND_ is the tissue free fraction of non-protein bound ^11^C-SB207145, Bavail is the concentration of available 5-HT_4_R and K_D_ is the dissociation constant for the tracer at equilibrium. Thus, BP_ND_ is proportional to the density of 5-HT_4_R.

#### MRI and fMRI Imaging

All participants are screened for MR-compatibility and thoroughly instructed how to perform the fMRI paradigms by a trained study assistant who uses standardized instructions. All MRI scans for patients will be acquired using the same Siemens 3-Tesla Prisma scanner with a 64-channel head coil. High-resolution structural T1- and T2-weighted MR images will be acquired. Blood oxygenation level dependent fMRI scans will be obtained during a commonly used emotional faces paradigm (85, 86), reward-related guessing paradigm (87, 88) and a 10-min rs-fMRI scan. During the rs-fMRI scan, participants are asked to close their eyes, let their mind wander and to not fall asleep. All structural scans of patients will be screened for pathological abnormalities by a medical specialist in radiology.

#### EEG

EEG data is recorded using a 256-channel HydroCel Sensor Net system (EGI, Inc., Eugene, OR) at 1,000 Hz with 0.1–100 Hz analog filtering where vertex electrode serve as the reference. Impedances across all electrodes are kept below 50 kΩ. EEG/ERP recording at baseline included: resting EEG (with eyes closed and open), two-tone auditory oddball and the LDAEP tasks. The same EEG/ERP recording will be re-tested in a subgroup of patients after 8 weeks of treatment.

##### Resting EEG

Resting EEG is recorded during four 3-min periods with a counterbalanced order of OCOC (O for eyes open, C for eyes closed) or COCO between subjects. Participants are instructed to remain still and relax, avoid eye-blinks and movements and to relax chin muscles during recording. Absolute and relative powers are computed using the following frequency bands: δ (1–4 Hz), θ (4–8 Hz), α (8–12 Hz), and beta (8–30 Hz). In addition, alpha peak frequency (APF) is identified by the frequency at maximal absolute power from the spectral range of 7–13 Hz. Frontal alpha asymmetry will be calculated using alpha power with the formula of (F4 – F3)/(F4 + F3) (Arns et al., 2015). Furthermore, theta activity will be extracted from anterior cingulate cortex with exact low-resolution electromagnetic tomography (eLoreta).

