EEG, a monitoring technique for direct ongoing neural activity, has been reported to be associated with treatment response in MDD [see, e.g., review (29)]. Prior studies have found that treatment responders have higher cortical alpha activity (30) and higher theta activity at rostral anterior cingulate cortex compared to treatment non-responders (31, 32). Of note, these biomarkers were derived from the resting EEG data, which is relatively easy to implement in the clinic. Furthermore, earlier evidence from event-related-potential (ERP) studies have suggested that ERP biomarkers such as auditory P300 (a positive waveform around 300 ms after stimulus onset) and loudness-dependence of auditory evoked potentials (LDAEP) can be predict drug treatment response (33, 34), and are linked to the serotonergic transmitter system (35). In the current trial, the predictive values of pretreatment EEG/ERP biomarkers will be examined.

Disturbances in cognitive processes including memory, attention, and executive functions are commonly reported in MDD (36) and contribute to psychosocial impairment and workforce disability (37). In addition, affective bias in information processing (i.e., favoring negative information over positive information at different levels of information processing) has been proposed as a central mechanism in the development and maintenance of depressive symptoms (38) which is also predictive of later treatment response to antidepressant drugs (39). Notably, cognitive disturbances do not always resolve with the remission of a depressive episode, suggesting a dissociation between core mood and cognitive symptoms in MDD (40). Combined with the low cost and relative ease of testing in a clinical setting, this distinguishes cognitive disturbances as a promising marker for stratification of depression subtypes as well as an important target for antidepressant treatment. In the present study, we therefore aim to map a broad range of cognitive disturbances in MDD, including both cold (non-emotional) and hot (emotional) cognitive processes, and explore whether they may be used to characterize clinically relevant subgroups in MDD. Based on earlier observations in healthy individuals, we expect memory performance to map onto hippocampal 5-HT_4_R availability (41) and possibly affective bias in verbal memory in MDD (42).

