#### Predictive Value of the Biomarkers Across Modalities

Two strategies will be considered to optimize prediction of treatment response using biomarkers measured at baseline across modalities. In the first strategy, we will combine the specific biomarker-candidates across all modalities (as predefined in **Appendix 1**), which will generate around 50 candidate biomarkers. A dimension reduction step will be used to define a small number of predictors (roughly 5–10) that will be used in a logistic regression model. The second strategy will use an algorithm to (i) identify, in a data-driven way, biomarkers with a predictive value among all the existing biomarkers (roughly 5,000–10,000) and (ii) predict treatment response based on the identified subset of informative biomarkers. We will investigate the use of machine learning methods (e.g., random forest, neural networks) as well as ensemble methods [e.g., Super Learner (116)]. The assessment of the predictive performance of these strategies will be carried out as described in the previous section.

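### The resting EEG beta band is set at 8–30 Hz and contains the whole 8–12 Hz alpha band, so beta power cannot be separated from alpha power

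*Protocol article*

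**What the plan says.** The Resting EEG section of the Protocol article fixes the measurement in one sentence: "Absolute and relative powers are computed using the following frequency bands", followed by "δ (1–4 Hz), θ (4–8 Hz), α (8–12 Hz), and beta (8–30 Hz"). Delta ends where theta starts and theta ends where alpha starts. Beta does not start where alpha ends. No other section gives a different lower limit for beta or says that the overlap is intended, and the section does not name the denominator for relative power.

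The same section defines two alpha-based measures separately: "alpha peak frequency (APF) is identified by the frequency at maximal absolute power from the spectral range of 7–13 Hz", and a frontal asymmetry index built from alpha power at F3 and F4.

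On use, the Introduction says that "the predictive values of pretreatment EEG/ERP biomarkers will be examined". It motivates alpha activity and anterior cingulate theta from earlier studies and does not mention beta. The section on prediction across modalities adds a data-driven search for "biomarkers with a predictive value among all the existing biomarkers (roughly 5,000–10,000"), a pool that could include beta power. The predefined candidates are in Appendix 1, which is not shown.

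**The concern.** Band powers are useful as separate variables only if each covers its own part of the spectrum. With "α (8–12 Hz), and beta (8–30 Hz"), every unit of alpha power is also a unit of beta power. A patient with high alpha would then tend to show high beta even if activity above 12 Hz were ordinary. If beta as defined were associated with remission, nobody could say from that result whether the signal came from alpha or from faster activity.

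Relative power raises a second issue. If each band is divided by the sum of the four listed bands, the 8–12 Hz power is added twice. The denominator is then inflated by an amount that depends on the patient's own alpha, and the error reaches relative delta, theta and alpha as well as beta. Alpha and theta are the two bands that the Introduction motivates. The article also offers the dataset for cross-validating predictors found elsewhere, so the published limits need to be ones that others can reproduce and compare.

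**Working it through.** **Inputs from the article (Resting EEG).** Delta 1–4, theta 4–8, alpha 8–12, beta 8–30 Hz, with absolute and relative power in each. The article reports no band powers or spectra, so there is no figure of its own to reproduce.

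**Step 1: overlap by width.** Alpha is 12 − 8 = 4 Hz wide and the stated beta band is 30 − 8 = 22 Hz wide. Alpha lies wholly inside beta and makes up 4/22 = 18% of it.

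**Step 2: overlap by power.** Let A be the power in 8–12 Hz, B the power in 12–30 Hz, and T the power in 1–30 Hz.

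- Beta as written = A + B.
- Alpha's share of it = A/(A + B).
- Sum of the four listed bands = T + A. Define S = (T + A)/T = 1 + A/T.

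The spectrum has to be assumed. The working one is f^(−k) plus a Gaussian peak at 10 Hz (SD 1 Hz) with height h times the local background. With no peak the share has a closed form:

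- k = 0: 4/22 = 0.18
- k = 1: ln(12/8)/ln(30/8) = 0.405/1.322 = 0.31
- k = 2: (1/8 − 1/12)/(1/8 − 1/30) = 0.0417/0.0917 = 0.45

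Numerical integration gives the other cells. Each shows alpha's share of 8–30 Hz power, then S:

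| k | h = 0 | h = 1 | h = 3 | h = 10 |
|---|---|---|---|---|
| 0 | 18%; 1.14 | 26%; 1.20 | 38%; 1.31 | 60%; 1.52 |
| 1 | 31%; 1.12 | 41%; 1.18 | 55%; 1.27 | 74%; 1.47 |
| 1.5 | 38%; 1.08 | 49%; 1.12 | 62%; 1.19 | 79%; 1.37 |
| 2 | 45%; 1.04 | 56%; 1.07 | 69%; 1.11 | 83%; 1.23 |

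The share runs from 18% to 83%. It passes one half only when there is a clear peak.

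**Step 3: built-in correlation.** A and B were simulated as independent lognormal variables across patients (assumed log-scale SD 0.5 or 0.8 for A, 0.5 for B), so the true correlation of log A with log B is 0. The correlation of log A with log(A + B) was then:

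- 0.25–0.40 at an 18% share
- 0.69–0.82 at a 50% share
- 0.89–0.94 at a 70% share

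With beta limited to 12–30 Hz, the correlation in the same simulation is about 0.

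**Step 4: relative power under two possible denominators.**

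- *Total 1–30 Hz power, T.* Relative delta, theta and alpha are correct. Relative beta is (A + B)/T instead of B/T, and the four values add to S, which is 1.04–1.52 in the table.
- *Sum of the listed bands, T + A.* The four values add to 1, but relative delta, theta and alpha are each divided by S. They shrink by 1 − 1/S: from 1 − 1/1.04 = 4% to 1 − 1/1.52 = 34%. The shrinkage varies between patients because A/T does.

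**The case against.** The case against giving this much weight is good on several points.

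- *A reader might infer that beta would largely re-measure alpha.* The documents do not support that. By width alpha is 18% of the band, and without a spectral peak it is a minority of the power for every background tried. A marked alpha peak is plausible, since eyes-closed rest is recorded and an alpha peak is sought, but no spectrum is reported.
- *A reader might infer that the four relative powers must add to more than 1.* That needs a fixed 1–30 Hz denominator, which the article does not state. Over the sum of the listed bands they add to exactly 1. Over a wider recorded range (the analog filter is 0.1–100 Hz) the sum could fall below 1.
- *A reader might infer damage to multiplicity control or to the combined models.* The overlap does not change the number of tests, and correlated tests make a Bonferroni-type correction conservative. Within a modality, prediction uses one biomarker with clinical data. Across modalities, one strategy reduces dimension first and the other uses learners meant for many correlated inputs. One more correlated pair matters little there.
- *Beta is not named as a predictor in the text shown.* Its place in Appendix 1 cannot be checked.
- *The limit may be a misprint.* The article defers a fuller EEG description to later reports, and the script may already be right.

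These points narrow the consequence. They do not remove the error: the article states the limit, the limit is operative, and a promise of later detail does not correct it. Whatever method uses beta, a result for it could not be attributed to activity above 12 Hz.

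**Conclusion.** The beta definition is wrong as written. It places all alpha power inside beta, makes the two correlated by construction, and prevents a beta finding from being separated from an alpha finding. That follows from the stated limits alone.

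The size does not. Alpha's share of the stated beta band is 18% by width and about 18–83% by power, and the induced correlation ranges from modest to near complete. Both ranges rest on the assumed spectra and between-patient spreads in the working. The 4–34% shrinkage of relative delta, theta and alpha applies only if the denominator is the sum of the listed bands.

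The reach is limited to resting EEG beta power and, depending on that denominator, the relative powers. Absolute delta, theta and alpha power, alpha peak frequency and frontal asymmetry have their own definitions and stand. The primary clinical outcome, the PET latent variable analysis and the sample size are not affected.

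**What to change.** - Restate the beta band so that it does not overlap alpha. A 12–30 Hz band follows the article's own end-to-end pattern and lets the four bands cover 1–30 Hz once.
- State the relative-power denominator and make sure that it counts each frequency once. Which total is used is a choice for the investigators.
- Check the limits coded in the processing script before EEG predictors enter any analysis. If the script already uses a non-overlapping band, only the text needs correcting. If it uses 8 Hz, re-run band power on the recordings already held and replace the affected variables.
- State the corrected limits in the fuller EEG report that the article announces.

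The cost is one number and one sentence in the text and, at most, a re-run of the band-power step. No patient procedure or recording changes.

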##### Task Elicited ERPs

The two-tone auditory oddball paradigm consists of two acoustic stimuli with different frequencies. Participants are presented with a series of standard tones (500 Hz) and deviant tones (1,000 Hz) binaurally through inserted earphones (Etymotic Research Inc., ER 3C). They are instructed to press a button when the deviant tones are presented while ignoring the standard tones. ERP components such as N1 and P3 will be computed, both peak latency and amplitude (baseline to peak) will be extracted by the averaged trials. Participants are presented with five acoustic stimuli with different intensities (60, 70, 80, 90, and 100 dB SPL) in the same frequency of 1,000 Hz. No response is needed. The primary outcome is the slopes of peak-to-peak N1/P2 amplitudes extracted from the average trials at each intensity. A more comprehensive description of the EEG data will be presented in the subsequent reports.

#### Cognitive Testing

All participants undergo cognitive testing using selected tasks from the novel test battery EMOTICOM, assessing affective and social cognition including emotional face recognition, emotional threshold detection, theory of mind, and moral emotions (89). In addition, affective memory (90), working memory, reaction time and IQ will also be assessed. Testing is planned and conducted by trained neuropsychologists prior to start of drug intervention and again after 12 weeks of treatment.

#### Psychometrics

Apart from clinical visits including HAMD_17/6_ ratings, patients will apply self-monitoring during the study period and fill out Danish versions of online questionnaires throughout the study. All questionnaires will be imported directly to an internal database through LimeSurvey, a free and open source software. Before EEG scans and cognitive testing, all participants will report their current mood state using an in-house Likert-scale. An adjusted Likert-scale will be filled out after each MR-scan. During visits at week 4, week 8, and week 12, patients are also asked to fill out a comprehensive set of self-rating state questionnaires (see **Table 1** for a full overview). Healthy controls will be asked to fill out selected state questionnaires as part of their baseline assessments.

**Table 1 T1:** Table over questionnaires obtained throughout the study.

Questionnaires	Time point					
	Baseline	Week1	Week 2	Week 4	Week 8	Week 12
**MINI**	X					
**HAMD-17/6**	X	X	X	X	X	X
**UKU**		X	X	X	X	X
**NEO-PIR**	X					
**CATS**	X					
**EHI**	X					
**OS-FHAM**	X					
**PBI-mother/father**	X					
**POMS***	X				X	X
**Likert-scale***	X				X	X
**BDI-II**	X			X	X	X
**MDI**	X			X	X	X
**PSS**	X			X	X	X
**SHAPS**	X			X	X	X
**RRS**	X			X	X	X
**CSFQ_F_C**	X			X	X	X
**SUSY item 32**	X			X	X	X
**Activity**	X			X	X	X
**GAD-10**	X			X	X	X

Trait questionnaires at baseline includes personality traits with NEO-PIR (91); Child Abuse and Trauma Scale (CATS) (92) a survey about early life stress which has shown to be able to modulate the serotonin system in the brain (93); handedness with Edinburgh Handedness Inventory (EHI) (94); an in-house version of the Family History Assessment module (FHAM) questionnaire, i.e., “Online Stimulant” (OS)-FHAM; Parental Bonding Inventory (PBI) (both mother and father) (95). State conditions included a self-rating questionnaire of Profile of Mood States (POMS) (96); an in-house Likert-scale; Beck’s Depression Inventory-II (BDI-II) (97); Major Depression inventory (MDI) (98); Cohen’s Perceived Stress Scale (PSS) (99, 100); Snaith-Hamilton Pleasure Scale (SHAPS) (101); Rumination Response Scale (RSS) 102; Changes in Sexual Functioning Questionnaire (CSFQ) (103); “Sundhed og Sygelighed” Sex Quality Questionnaire item 32 (SUSY-item 32) (104); an in-house questionnaire about daily physical activity (71); and Generalized Anxiety Disorder-10 (GAD-10) (105). * Collected in immediate extension to EEG and MR examinations or cognitive testing.

#### Biomaterials

##### Blood

At baseline, all participants will be screened for basic somatic status to exclude somatic conditions with possible influence on depressive symptoms. Blood samples will be collected throughout the study (see **Table 2** for a full overview) for determination of inflammatory status (high sensitivity C-reactive protein, tumor necrosis factor-α, Interleukin-6, -18, and -10) (106–109); epigenetic variations (SERT, FKBP Prolyl Isomerase 5, Catechol-O-Methyltransferase (COMT), monoamine oxidase-A, glucocorticoid-, estrogen-, oxytocin receptor and oxytocin gene-methylation); extraction of DNA for genotypes of relevance (rs41271330 (110), serotonin-transporter-linked polymorphic region (5-HTTLPR) (70), COMT, Brain-Derived Neurotrophic Factor val66met) and ABCB1, FZD7, and WNT2B (that presumably influence responsiveness to pharmacological antidepressant treatment (111)). At week 8, serum samples of the antidepressant drug (i.e., escitalopram or duloxetine) are collected as trough concentrations in steady state, with primary purpose of monitoring compliance. The samples will be stored at −20°C (or −80°C for plasma EDTA samples) until analyzation in batches at completion of the trial. Quantification of escitalopram and duloxetine in serum will be performed at the Laboratory of the Danish Epilepsy Centre, Filadelfia, using a routine UPLC-MS/MS method developed in-house. Standard operating procedure instructions have been established before trial initiation and will be followed during the assessment of all biomaterial.

**Table 2 T2:** Somatic status and biomaterial assessed at various timepoints throughout the study.

Analysis	Sample	Timepoint		
		Baseline	Week 8	Week 12
Somatic blood-sample screening	Hemoglobin, white blood cell count, metamyelo.+myelo.+promyelocytes. C-reactive protein.	X	X	X
	Na+, K+, Creatinine	X		
	ASAT, ALAT, GGT, LDH, BAP	X		
	Albumin, Coagulation factors II+VI+X, thrombocytes	X		
	B12, Folate	X		
	25-OH-vitamin D	X		
	Blood sugar, HbA1c	X		
	Triglycerides, total-cholesterol, HDL, LDL	X		
	TSH, Ionized Calcium	X		
	Estradiol, testosterone, progesterone, FSH (females)	X		
Somatic examination	Electro Cardiogram (ECG) Neurological status Somatic status	X X X		
Compliance to medicine control	S -escitalopram or S -duloxetine		X	
Biobank	Inflammation and cytokines (hsCRP, TNF-α, IL-6, IL-18 and IL-10)	X	X	X
Biobank	Epigenetics (5-HTT, glucocortocoid-, FKBP5, COMT, MAO-A, estrogen-, oxytocin receptor and oxytocin gene-methylation)	X	X	X
Biobank	Genotypes (rs41271330, 5-HTTLPR, COMT, BDNFval66met)	X		
Biobank	Gene transcription profiles (mRNA and microRNA, ABCB1, FZD7 and WNT2B)	X	X	X
Oxidative stress	Urine (8-oxo-dG and 8-oxo-Guo)	X	X	
Biobank	Saliva (Cortisol awakening response)	X	X	

##### Saliva

Saliva will be collected to determine the total cortisol output across one day as well as dynamics of the HPA-axis, as indexed by CAR. Serial saliva samples will be sampled at home and collected at baseline and at week 8 (see **Table 2**). Those visits will be placed as close to the PET-scan day or week 8 visit as possible, and patients are instructed to take samples immediately after awakening and again after 15, 30, 45, and 60 min, at 12, 6, and 11 pm. Participants are also instructed to collect saliva samples preferably during weekdays, not perform strenuous exercise <2 h and not to have any oral intake or brush their teeth <1 h prior to sampling. Cohen’s Perceived Stress Scale and basic information about sleep and food intake will be filled out in conjunction with the home-sampling. All participants receive careful training in saliva collection, instructions of home-sampling procedures; cold storage of samples and fast delivery either by mail or personal delivery to the laboratory facility for preparation. When received, salivary test-tubes are centrifuged and stored at −80°C until later single-batch analysis.

